#### Other considerations

Participants in both the intervention and control groups are free to undertake additional professional development or supervision at their discretion. At the conclusion of the trial, these additional activities will be recorded.

Participants will be free to withdraw from both intervention and follow-up activities. They will be sent an email from a member of the research team (not the first author, who will be delivering aspects of the intervention) and asked to provide a brief reason for their withdrawal, as this information is useful to inform recruitment and retention of participants in the future trial. The point of withdrawal will be documented, and participants will be advised in the consent form that data gathered up until the point of withdrawal will remain available to the investigators for analysis.

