#### Secondary outcomes

Acceptability of trial processes to participants will be measured by a study-specific survey following the pre-trial information session and at the end of the trial. Those who choose *not* to enrol in the trial following the information session will also be asked to complete the study-specific survey as to their reasons for non-participation, and a frequency count of responses to these multiple-choice items will be undertaken.

Clinician self-reported Capability, Opportunity and Motivation to use PCIT (drawn from COM-B theory; [23]) will be measured by Likert scale items within a monthly self-report survey, developed for the purposes of this trial and delivered via Qualtrics.

Acceptability of the monthly surveys as a data collection method, and the timing and frequency of these, will be measured by response rates. Also, a post-trial semi-structured phone interview will incorporate Likert scales and seek participants’ ratings of the acceptability of the monthly surveys as a data collection method.

Acceptability of each aspect of the re-implementation intervention will be assessed by participant uptake of the components. As an online booking system will be used to coordinate the loan of (1) the audio-visual equipment, (2) the time-out cubicle and (3) the mobile co-worker, a frequency count of weekly bookings will be used as a proxy measure for the acceptability of these items.

Also, in a post-trial semi-structured phone interview, participating clinicians will be asked to rate the acceptability of the components of the re-implementation package on a series of Likert scales. Acceptability of group consultation sessions will be assessed by participant attendance rates, measured by an audit of session attendance registers.

Clinician adoption of PCIT will be assessed by clinician self-report of the number of unique families to whom PCIT was delivered in the most recent representative 1-week period at 6 months post-randomisation and compared to baseline (via the study-specific monthly survey). Given that PCIT sessions are typically held weekly, this is expected to provide a valid measure of clinician PCIT adoption.

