Acceptability of the recruitment and trial processes to Māori clinicians will be assessed by multiple-choice items within a study-specific questionnaire following the pre-trial information session and at the end of the trial. Māori clinicians choosing not to enrol in the trial will also be offered the opportunity to speak kanohi-ki-te-kanohi (face to face) or via phone with a Māori research team member, to discuss their impressions and any concerns about trial recruitment processes and/or methodology that contributed to their decision not to participate, and this qualitative data will be recorded.

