### Statistical considerations

#### Sample size and justification

As this is a feasibility study, sample size calculations are not required, and a formal power calculation is not appropriate, given that the primary outcome for this pilot is feasibility [38]. Instead, sample sizes for feasibility studies should be based on pragmatic considerations [39]. However, for the RCT, it is envisaged that the primary outcome will be *adoption*: clinician self-report of the number of unique families to whom PCIT was delivered in the most recent representative 1-week period at 6 months post-randomisation, compared to baseline. These data will be collected.

Relevant pragmatic considerations included the size of the group of PCIT-trained clinicians thought to be practicing in the Tāmaki Makaurau/Auckland region, excluding the research team (approximately 70). Also, the budget for the research project will only support limited co-worker hours, and the purchase of limited time-out pop-up cubicles and limited audio-visual equipment and toy packages. Given these practical constraints, we hope to recruit 10 participants per condition or 20 overall. We are interested in evaluating whether the proposed recruitment methods will be effective in a future, larger trial. While we will aim to recruit this number, our ability to do so will provide valuable data around our ability to recruit sufficient participants for a fully powered trial using the described methods.

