#### Progression criteria

The following criteria will be used to assess whether it is feasible to progress to a fully powered randomised controlled trial in the future.Clinician recruitment rate: study is considered feasible if at least 20 clinicians enrol in the trial. Given that we have contact information for 70 PCIT-trained clinicians in the region (i.e. the population of interest), we consider this number to be reasonable.Clinician trial completion rate: study is considered feasible if there is a maximum of 20% attrition.Acceptability of surveys as a data collection method: study is considered feasible if the average survey response rate (across the baseline, monthly and end-of-trial surveys) is at least 80%.

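### Ratings of the components and monthly surveys are scheduled only after the trial, and none is specified for clinicians who withdraw, so they are likely to over-represent completers

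*Protocol article*

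**What the plan says.** All references are to the protocol article.

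- **Ratings of the package.** Under Secondary outcomes, "in a post-trial semi-structured phone interview, participating clinicians will be asked to rate the acceptability of the components of the re-implementation package". The same interview collects ratings of the monthly surveys as a data collection method. Table 2 schedules the interviews at the end of the trial only, for both arms.
- **Other acceptability measures.** Secondary outcomes also uses weekly booking counts (audio-visual equipment, time-out cubicle, co-worker), attendance at group consultation, and response rates to the monthly surveys. Trial processes are surveyed after the information session, including among those who do not enrol, and again at the end of the trial.
- **Withdrawal.** Other considerations states: "Participants will be free to withdraw from both intervention and follow-up activities". Those who leave are emailed by a team member not delivering the intervention and "asked to provide a brief reason for their withdrawal". The point of withdrawal is documented, and "data gathered up until the point of withdrawal will remain available to the investigators for analysis".
- **Māori clinicians.** Secondary outcomes states: "Māori clinicians choosing not to enrol in the trial will also be offered the opportunity to speak kanohi-ki-te-kanohi (face to face) or via phone". A member of the team who is Māori would hold this conversation. Other considerations describes no such offer for a Māori clinician who enrols and later withdraws.
- **Size and tolerance.** "we hope to recruit 10 participants per condition or 20 overall" (Sample size and justification); "study is considered feasible if there is a maximum of 20% attrition" (Progression criteria).

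**The concern.** Two of the five aims under Study aims depend on acceptability. One includes judging the intervention's acceptability to Māori participants. The other is to judge the package's acceptability to clinicians so that its components can be refined. Clinicians who found the package or the trial methods hard to accept may be more likely to leave, and what they could say about the components would be especially useful for refining them. The schedule collects ratings at a point they may not reach, and the contact described at withdrawal seeks a reason for leaving rather than a rating of each component.

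The treatment of Māori clinicians is also uneven. Someone who never joined is offered a conversation. For someone who took part and then left, the article describes only the general email. With few Māori participants expected, each lost response matters.

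The consequence is a set of ratings that may look better than the views of everyone randomised, with little to show which component should change.

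**Working it through.** **Inputs.** Target 10 per arm, 20 overall (Sample size and justification). Maximum attrition 20% (Progression criteria). Māori share 14.8% among PCIT-trained clinicians in the 2021 survey (Intervention). No acceptability rate is given or assumed in the article, so the rates below are assumptions, shown as a range.

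**Step 1: the plan's own figures.** 2 × 10 = 20. Tolerated withdrawals: 0.20 × 20 = 4, leaving 16 completers.

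**Step 2: what is held for a withdrawer.** Table 2, read by time point:

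| Time | Scheduled data | Rating after exposure to the package? |
|---|---|---|
| Information session | Trial-process survey | No, precedes allocation |
| Baseline | General data, adoption count, Theoretical Domains Framework questionnaire | No |
| Monthly | Adoption count, three capability/opportunity/motivation items, response rate | No |
| Weekly | Bookings, consultation attendance | No, behaviour only |
| Month 6 | Interview, trial-process survey | Yes |

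A clinician who leaves before month 6, and is not interviewed, has behavioural data but no rating.

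**Step 3: what the behavioural data leave out.** The toy pack is kept by the clinician and not booked (text following Table 1), so its only specified acceptability measure is the post-trial rating. For booked items, a low count is ambiguous, because the Intervention section expects that some clinicians will need only one or two elements.

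**Step 4: size of the bias.** Let a be attrition, p_c acceptability among completers and p_w among withdrawers, with every completer and no withdrawer rating.

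- All-participant value = (1 − a) × p_c + a × p_w
- Bias = p_c − that value = a × (p_c − p_w)

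At a = 0.20:

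| p_c | p_w | All-participant value | Bias (points) |
|---|---|---|---|
| 100% | 0% | 80% | +20 |
| 100% | 50% | 90% | +10 |
| 90% | 0% | 72% | +18 |
| 90% | 50% | 82% | +8 |
| 90% | 90% | 90% | 0 |
| 90% | 100% | 92% | −2 |

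The upper limit is 0.20 × (100 − 0) = 20 points.

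**Step 5: intervention arm alone.** Only this arm receives the full package. With 2 withdrawals, 8 raters remain and the upper limit is 2/10 = 20 points. If all 4 tolerated withdrawals fell in this arm, 6 raters would remain and the limit would be 4/10 = 40 points.

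**Step 6: Māori participants.** If the 14.8% share carries over, 0.148 × 20 = 2.96, about 3 in total. Half of these, 1.48, would be expected in the intervention arm. One withdrawal would remove about a third of the end-of-trial responses from Māori clinicians.

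**The case against.** The strongest reply is that acceptability does not rest on the interview. Uptake is the measure named first for the components, and the Likert ratings are added to it. Bookings, attendance and survey response rates accrue during the trial and are kept for those who leave, so a clinician who disliked a component and withdrew would appear as low uptake. Trial-process acceptability is also surveyed before enrolment. All of this stands. A reader might infer that acceptability as a whole comes from completers only; the article does not support that.

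Secondly, exclusion of withdrawers from the interview is an inference. The article names withdrawal from intervention and from follow-up without saying that leaving one ends the other, and it offers the interview to participating clinicians rather than to completers. This also stands, and it is a reason to make the text explicit.

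Thirdly, withdrawal need not mean dislike. The supports are optional, so a dissatisfied clinician can simply not book. A reader might infer that the ratings are shown to be biased upward; they are not, because withdrawers' views are unknown and the bias can be zero or slightly negative.

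Fourthly, the losses would be visible. Completion is a primary outcome, reasons are recorded, attrition has its own limit, and the ratings enter no progression criterion. This lowers the stakes, but a brief reason for leaving does not supply a view of each component.

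Finally, a journal article condenses the full protocol, which may provide an exit interview. Yet the article does set out both the withdrawal contact and the rating schedule, and the point concerns those stated procedures.

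**Conclusion.** The point holds in a limited form. Ratings of the components and monthly surveys, and end-of-trial views of trial processes, including those of Māori clinicians, are likely to over-represent completers, probably in the favourable direction. At the tolerated attrition the bias is at most 20 points overall. The 40-point limit for the intervention arm needs all four withdrawals to fall there.

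These limits assume that every completer rates, that no withdrawer does, and that the two groups differ as far as they can; realistic differences give smaller figures. The count of about 3 Māori participants assumes that the earlier survey's share applies to this sample.

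Retained uptake, attendance and response data offset the gap in part, but not for the toy pack, and they do not separate what was unacceptable from what was not needed. The feasibility decision is unaffected, since the only acceptability criterion for progression is the survey response rate. What is at risk is the evidence for the two acceptability aims. This is a worthwhile, inexpensive improvement rather than an error that undermines the trial.

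**What to change.** Amend Other considerations, with matching consent-form wording, as follows.

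1. At withdrawal, offer every clinician the existing acceptability Likert items, as a short online form or through the phone interview.
2. Offer withdrawing Māori clinicians the same conversation with a Māori research team member that Secondary outcomes gives to those who decline to enrol.
3. Record whether the clinician is stopping the supports, the follow-up or both. Those stopping only the supports stay in follow-up, including the end-of-trial survey and interview.
4. Report ratings for all randomised clinicians with any rating, beside completers only, together with uptake and withdrawal reasons.

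The cost is wording changes, reuse of instruments that already exist, and about four short voluntary contacts at the attrition limit. Some withdrawers will decline, so the gap will be reduced rather than closed.

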### Intervention and control conditions

#### All participants

All participants will undertake a 2-day refresher training, the content of which is informed by PCIT International’s ‘recalibration’ training, by previous research into implementation barriers encountered by clinicians in Aotearoa/New Zealand and culturally responsive practices. This complimentary, catered training will be delivered on two successive Saturdays, to facilitate clinician attendance regardless of their current employment context. It will be co-delivered by an experienced Māori PCIT provider and a senior PCIT trainer in Tāmaki Makaurau/Auckland and will only be delivered virtually if absolutely necessary due to COVID-19 restrictions.

Incorporated within the two training days, *all* participants will receive the following enhanced supports:A collection of resources to support delivery, including detailed virtual delivery resources and demonstration of these. Access to a Dropbox with all resources and materials.A voucher for a complimentary pack of 25 Eyberg Child Behaviour Inventory (ECBI; [33]) questionnaires to use with future PCIT clients, and a complimentary PCIT treatment protocol in the event that this has been misplaced since their initial PCIT training.Facilitated discussion and problem-solving sessions around using PCIT in various contexts including private practice should participants choose to do this. For example, what to charge for PCIT, how to obtain referrals and where suitable clinic rooms are located.Discussion, facilitated by a Māori PCIT provider, relating to how to deliver PCIT in a culturally responsive way.

After the two training days, *all* participants across both groups will be offered optional complimentary weekly 1-h group PCIT-oriented consultation with a senior PCIT clinician, for the 6-month trial period.

#### Intervention

Specific components of the intervention are provided in Table 1, according to the TIDieR checklist [34]. In summary, clinicians allocated to the intervention condition will receive the following:A pack of suitable PCIT *toys* to use with children and families, which will be provided free of charge.Access to a mobile *co-worker*/‘PCIT partner’ who can be booked through an online booking system free of charge at any time. This senior PCIT clinician will be available to join a client session to support the clinician (the clinician is responsible for obtaining client consent for this to occur), or to plan or debrief sessions, as requested by the clinician, and in any location of the clinician’s choice. We will recruit a senior Māori PCIT clinician to this role, as Māori are the Indigenous people of Aotearoa/New Zealand and a number of PCIT-trained clinicians are Māori (14.8% in our 2021 survey).Access to portable, relocatable *audio-visual equipment,* including a high quality digital remote camera and monitor, which allows viewing of the clinic room from a nearby room and a Bluetooth earpiece to facilitate clinician coaching of the parent(s) from the nearby room.Access to an in-room *time-out pop-up cubicle* to be used if the child requires a brief time-out, that is transportable to the participant clinician’s clinic room of choice.

**Table 1 Tab1:** Re-implementation intervention components, described using the TIDieR checklist

Brief name	Re-implementation support package for PCIT-trained clinicians
Why	PCIT is an effective treatment for childhood conduct problems, and a number of clinicians have received a five-day initial training in the approach since it was introduced to Aotearoa in 2010. Our earlier work suggests that, despite PCIT-trained clinicians viewing PCIT as effective and acceptable, relatively few are using it in their work, and those who are using it, are seeing a small number of families. The majority of PCIT-trained clinicians describe having encountered barriers to its use, which include lacking suitable equipment, and families having difficulty accessing clinic-based sessions. Facilitators of PCIT’s use included access to a suitable clinic room, and the ability to co-work PCIT cases with another clinician. These earlier studies have shaped the selection of intervention components, which have also been informed by the COM-B behaviour change theory
What	**Materials** • Participating clinicians will have access to a Dropbox folder of PCIT-related resources, including research articles, slides from relevant presentations, handouts and worksheets. These have been produced by a number of different PCIT researchers and clinicians • Clinicians will be provided with a toy package of approximately $NZD700 value, containing toys selected by two senior PCIT clinicians (Māori and non- Māori) as being suitable for use in PCIT • Two robust Voyager Compact travel bed tents from Safespaces UK (www.safespaces.co.uk) will be available for clinicians to book, to use as portable time-out spaces for children. Setup support will be provided to clinicians • Audio-visual equipment will include a ‘baby monitor’ kit, to allow remote camera viewing and audio from the adjacent room, by a clinician located in a separate space to the parent and child. A basic mobile phone and earpiece worn by the parent will allow clinicians to discretely provide coaching out of the child’s hearing **Procedures** • Refresher training content will be compiled and delivered by two senior PCIT-trained clinicians (Māori and non-Māori), one of whom is a Within-Agency Trainer for PCIT. It will include pre-existing video content from the UC Davis PCIT web course, and the Auburn University PCIT continuing education videos. The two trainers will also facilitate discussions and problem-solving sessions relating to how to deliver PCIT in a culturally responsive way, navigating client or colleague concerns relating to the use of time-out, and other topics that have been identified in our earlier research as impeding or influencing implementation. These discussions will be informed by the trainers’ own research and clinical experience
Who provided	The refresher training will be delivered by two PCIT-trained clinical psychologists, one of whom is Māori, and one of whom is a PCIT International accredited Within-Agency Trainer. The co-worker is an accredited PCIT provider, a Māori clinical psychologist. The weekly PCIT consultation groups will be facilitated by the first author, with support from the co-worker, who will also attend
How	Refresher training will be delivered in person. Weekly PCIT consultation sessions will be delivered in a hybrid format, where clinicians can join via Zoom or in person, according to their preference. Co-working contacts may involve the co-worker joining a client session (client consent having been obtained by the participating clinician in advance) or in person contact
Where	Refresher training will occur at a University clinic training room, over two successive Saturdays. Co-working will occur at a location of the clinician’s choice (e.g. their office, a Zoom call)
When and How Much	Refresher training ‘dose’ is fixed at two 8-h days, that will be scheduled approximately 6 weeks after the trial information sessions. PCIT consultation groups will occur weekly, for 1 h, across the 6-month trial period. Co-worker contacts are not fixed and are unlimited, and the uptake of this component is of interest as a study outcome
Tailoring	The re-implementation intervention will not be adapted or personalised by the research team; however, participating clinicians will select additional components that are of interest or relevance to them, using the online booking system. These additional components include (1) audio-visual equipment, (2) time-out pop-up tents, and (3) access to a co-worker
Modifications	N/A for protocol
How well	Intervention fidelity and adherence will not be assessed

These components will be available immediately after the refresher training, for the 6-month trial period. The toy package will be held by the individual participating clinicians, and all other components booked through an online booking system.

Given that there is uncertainty as to the extent to which an in vivo consultant aids clinician implementation of PCIT relative to the provision of equipment, we considered separating these components and investigating the influence of each on implementation. However, in practice, the co-worker (a senior PCIT clinician) is likely to discuss equipment, session logistics and clinic room setup in their interactions with the clinician participants while co-working sessions. As such, and given the pragmatic nature of this pilot trial, we have elected to combine these.

We also considered fitting-out a specialised clinic room in Tāmaki Makaurau/Auckland; however, one location may not be convenient for all participants, who are located throughout the city. Also, one centralised clinic room is less flexible and less scalable than a collection of modifiable supports. For example, a participating clinician may choose to implement PCIT in the client’s home, or in their existing workplace/agency, and/or may only require one or two elements from the package.

